**Discussion:**

This study will determine whether an 8-week outpatient based supervised exercise training program is safe and beneficial for medically stable PH patients in the short and long term. This will be the first study to examine the impact of exercise training on right heart function using exercise CMRI. Results from the study will contribute new knowledge in relation to the impact of exercise training on cardiac function, long-term prognosis and inform clinical practice guidelines for this patient population. Moreover, the study will add to our understanding regarding the efficacy of exercise training in individuals with PH in an outpatient setting.

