### Intervention group

Participants randomly allocated to the intervention group will participate in an 8-week, twice weekly outpatient supervised exercise training program. The exercise training program will be conducted in an outpatient rehabilitation setting and supervised by an experienced physiotherapy clinician who will closely monitor the participants’ exercise performance and provide appropriate exercise progression. Details of exercise training sites can be obtained at the Clinical Trial Registry ACTRN12616001467426.

The aim is for each participant to complete 20 min each session of cycling and treadmill exercises (40 min in total). Each participant will commence training in the first session by undertaking a minimum of 10 min of cycling and 10 min of treadmill training. Interval training, consisting of 60 s of exercise and 120 s of rest, will be used if participants are unable to complete 10 min of continuous exercise. The duration of cycling and treadmill exercises will be up-titrated such that participants are completing 20 min each session of cycling and treadmill exercises by the end of the second week.

The initial treadmill speed will be set at 60–70% of six-minute walk test (6MWT) speed and titrated up to 90% of 6MWT speed as tolerated over the first 4 weeks of training, by monitoring training heart rate (HR), rating of perceived exertion (RPE) and leg fatigue on the modified Borg scale will be determined. Training intensity will be maintained at this HR and RPE for the remainder of the 8-week training period. An upper limit for exercise intensity will be set at 85% of age-predicted maximum HR and 4 on the 0–10 modified Borg RPE scale. Cycle intensity will be calculated using the 6MWT distance from standard equations [21]. The initial cycle training intensity will be prescribed at 60% of the estimated peak work rate from the 6MWT distance.

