### Control group

The control group participants will continue with their routine medical care and physical activity regimes for the 8-week study period without the additional exercise training intervention. During the 8-week period, participants allocated to the control group will receive a weekly phone call from the study coordinator to review any adverse events and to record exercise habits.

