### Outcome measures

Baseline participant information including age, gender, anthropometrics (height and weight), co-morbid conditions and concomitant medications will be collected at the initial visit. In addition, various outcome measures will be undertaken at baseline, during and at completion of the 8-week study period. Clinical worsening will also be monitored for a minimum of 2 year period following commencement of the study (see below). All outcome measurements will be performed by a researcher blinded to the participants’ group allocation.

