Cardiac function will be measured using both cardiac magnetic resonance imaging (CMRI) and echocardiography, with CMRI serving as the principal method. Left and right ventricular end-diastolic volume and end-systolic volume will be measured using CMRI (1.5 T Scanner, MAGNETOM Aera, Siemens Healthcare, Erlangen, Germany) from which stroke volume, ejection fraction, cardiac output and contractile reserve will be derived [28]. In addition, measures of both right and left ventricular mass will be obtained. These will be measured at rest and during 2 submaximal exercise intensities (at 30% and 60% of their respective peak workload determined from incremental exercise test) using the MRI cycle ergometer. During the CMRI, electrocardiogram (ECG) and SpO_2_ will be continuously monitored and the test will be supervised by a medical practitioner. Echocardiographic evaluation will be performed as part of standard clinical protocol on the same day of the 6MWT. This will be assessed both at baseline and following the 8-week study period. Echocardiographic images will be acquired using a 4 MHz matrix array cardiac transducer (Vivid 7, General Electric, Milwaukee, Wisconsin, USA). All images will be attained with the participant in a semi-recumbent position for both the apical and parasternal windows. Right ventricular systolic pressure will be estimated from the tricuspid regurgitation velocity as per standard guidelines [29]. Right ventricular systolic function will also be examined by assessing the tricuspid annular plane systolic excursion.

Adverse responses or events including syncope, dizziness or marked worsening in oxygen desaturation during exercise will be monitored and recorded for the duration of the 8-week exercise training period. Such adverse events will also be assessed with weekly phone calls and recorded for the participants in the control group during the 8-week study period.

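### Eight-week adverse events are ascertained differently in the two arms, so a raw comparison would be confounded with detection, and the blanket blinding statement cannot cover them

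*Protocol article*

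**What the plan says.** Under Secondary outcome measures the article names the events: "Adverse responses or events including syncope, dizziness or marked worsening in oxygen desaturation during exercise". In the exercise arm these "will be monitored and recorded for the duration of the 8-week exercise training period". That arm attends an "8-week, twice weekly outpatient supervised exercise training program" (Intervention group), run by a physiotherapist, with heart rate, oxygen saturation and perceived exertion monitored in each session.

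For controls the route is different: "Such adverse events will also be assessed with weekly phone calls and recorded for the participants in the control group". The Control group section says who makes contact and why: each control participant "will receive a weekly phone call from the study coordinator to review any adverse events and to record exercise habits". Neither section states a call, or any other scheduled enquiry, for the exercise arm.

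The Outcome measures section says of assessment generally: "All outcome measurements will be performed by a researcher blinded" to allocation. Adverse responses stand among the secondary outcomes, and the Methods paragraph of the Abstract lists them among the measurements. The Discussion paragraph of the Abstract says the study will determine whether the programme "is safe and beneficial for medically stable PH patients in the short and long term".

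**The concern.** Recorded adverse events depend on how often they occur and on how well they are looked for. Here the second differs by arm in method (observation against self-report), frequency, assessor and what can be detected at all. A difference in counts, or the absence of one, could then come from ascertainment alone.

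Safety appears in the objectives, the hypothesis and the specific aims. The Background says that worry about serious adverse events is why exercise has not routinely been encouraged in this disease. Collecting the same kind of event in controls invites readers to set the two counts side by side.

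The blinding sentence adds a second problem. It would let the adverse-event data be reported as blind when the people collecting them know the allocation.

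**Working it through.** **1. The two routes side by side (Intervention group, Control group, Secondary outcome measures)**

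| | Exercise arm | Control arm |
|---|---|---|
| Route stated | Monitored and recorded over the training period | Weekly phone call |
| Contacts in 8 weeks | 8 × 2 = 16 supervised sessions | 8 × 1 = 8 calls |
| Who collects | Supervising physiotherapist (implied by the session description) | Study coordinator |
| Syncope, dizziness | Observed or reported | Reported from memory |
| Marked desaturation on exercise | Seen on oximetry | Not detectable by phone |
| Scheduled weekly enquiry | None stated | Stated |

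**2. Blinding.** A physiotherapist running the sessions knows the participant is in the exercise arm. A coordinator whose calls are stated for controls only knows the person called is a control. The outcome belongs to the list that the blinding sentence covers, so the sentence is incorrect for it.

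**3. Participants who stop training.** The Intervention group section says training is discontinued for those who suffer an adverse event. The Data analysis section includes all measures in available participants whether or not they completed the intervention. The sessions are the only contact described for the exercise arm during the 8 weeks, and the article does not say how events are collected once they end.

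**4. Size of the distortion.** The article gives no adverse-event rate, margin or power, so there is no stated figure to reproduce. What follows is illustrative.

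Inputs: 50 participants at 1:1, so 25 per arm (Sample size and power calculations; Randomisation). Assumptions: the same true risk p in both arms, full detection in the exercise arm (s_ex = 1), and control detection s_ctl of 0.80, 0.50 or 0.25.

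Observed risk ratio = (p × s_ex)/(p × s_ctl) = 1/s_ctl, whatever p is:
- 1/0.80 = 1.25
- 1/0.50 = 2.0
- 1/0.25 = 4.0

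The chance of a nominally significant false excess in the exercise arm (two-sided 5% test of two proportions) is approximately Φ[(d − 1.96 × se0)/se1]. Here d is the difference in observed risks, se0 the pooled and se1 the unpooled standard error. For p = 0.20 and s_ctl = 0.50:
- observed risks 0.20 and 0.10, so d = 0.10 and the pooled risk is 0.15
- se0 = √(0.15 × 0.85 × 2/25) = 0.101
- se1 = √(0.20 × 0.80/25 + 0.10 × 0.90/25) = 0.100
- Φ[(0.10 − 1.96 × 0.101)/0.100] = Φ(−0.98) = 0.16

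| True risk | s_ctl 0.80 | s_ctl 0.50 | s_ctl 0.25 |
|---|---|---|---|
| 10% | 4% | 10% | 19% |
| 20% | 6% | 16% | 36% |
| 40% | 8% | 33% | 70% |

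With equal detection the nominal figure in that direction is 2.5%. The approximation is rough with so few events. Summing binomial probabilities over all tables in which Fisher's exact test gives p < 0.05 with an exercise-arm excess, a true risk of 20% gives 3%, 9% and 20%. The risk ratio is distorted by the same amount whichever test is used.

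For exercise desaturation s_ctl by phone is zero, so any total that includes it is raised in the exercise arm only.

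**The case against.** Much of the asymmetry comes with the intervention. Supervised sessions are the treatment, controls have none to observe, and the weekly call looks like an attempt to narrow the gap. This stands. The correctable part is the lack of a stated enquiry common to both arms.

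A reader might infer that the trial promises a between-arm safety comparison it cannot deliver. The text does not go that far. The Background and Abstract ask whether training is safe, and the closing Discussion speaks of training-related adverse effects, which session monitoring can describe within the exercise arm. Data analysis names a group comparison for survival and clinical worsening but no test specific to adverse events. Recording the same events in controls implies a comparison without promising one.

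Nor is a comparison out of reach altogether. Syncope and dizziness can be reported by phone. Clinical worsening is assessed in both arms at routine visits and judged by a blinded panel, although the article calls the long-term outcomes underpowered. Oxygen saturation is also monitored during the cardiopulmonary test in all participants before and after the 8 weeks, though desaturation there is not named as an outcome. A safety board reviews the trial. None of this equalises the 8-week event count, but it shows that not all safety evidence is affected.

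A reader might also infer that exercise-arm events at home go under-recorded. That rests on silence. The article does not confine recording to events seen in sessions, and the physiotherapist could ask at each visit. Event forms and scripts are commonly left to the full protocol.

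Finally, the blinding sentence may have been meant only for tests such as the walk, imaging and exercise test. As worded it covers all outcomes, so it needs correcting.

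**Conclusion.** The point holds in limited form. As described, ascertainment of the 8-week adverse events differs by arm, and a raw between-arm comparison of them would be confounded with detection. The blinding sentence is wrong as written for this outcome.

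The size cannot be fixed from the article. The risk ratios of 1.25 to 4.0 rest on assumed detection rates and equal true risk. Their direction assumes that sessions find more than calls do. For events outside sessions the bias would reverse if only controls were actively asked, but the article does not establish that.

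The small number exposed might tempt a reader to add that 25 exercise participants cannot show safety. That concerns precision and would be the same under perfectly matched collection, so it lends no weight here. The primary outcome, sample size, stated power and Type I error are unaffected. This is an inexpensive improvement to a secondary outcome, together with one statement to correct.

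**What to change.** - Make the same scripted weekly adverse-event enquiry in both arms for the full 8 weeks, by call or by checklist, and continue it for exercise participants whose training has been discontinued.
- Limit any between-arm comparison to events from that common enquiry.
- Report session-observed events and desaturation separately and descriptively for the exercise arm.
- In the Outcome measures section, except adverse events from the statement on blinded measurement and say who collects them.

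Cost: 8 weeks × 25 exercise participants = 200 short contacts by existing staff, fewer as separate calls if a checklist is completed at sessions already attended, plus a wording change. If the full protocol already specifies a common enquiry, only the article's wording and the blinding sentence need to change.

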### Data analysis

Individual data will be de-identified, coded and entered into a password protected, secure database. The group allocation for each individual participant will be stored in a separate file at the time of allocation. Data will be double entered and range checks made on values to ensure data integrity. On completion of the study, the primary investigator (PI) will have access to the final trial dataset. An intention-to-treat analysis will be used to avoid bias in estimating the treatment effect for this superiority study, with inclusion of all measures in all available participants, regardless of whether they completed the intervention. We will use a generalised linear mixed model approach which can accommodate missing data points often encountered in longitudinal datasets and provides an ideal way of dealing with missing values or dropouts [33]. Equivalent parametric and non-parametric tests will be conducted where data does not meet normative assumptions. Probability of a Type I error will be set at 0.05. Survival and clinical worsening (event-free survival) will be estimated by the Kaplan-Meier method, using a stratified log-rank test for group comparisons. The commencement of the exercise program or control period will be used as the index date for determining survival or clinical worsening. Participants who have no clinical worsening event will be included up to their first clinic visit after the 2-year period study commencement.

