Currently, the evidence base of high quality studies examining exercise training remains narrow [15]. To date, the results of only 4 small RCT’s have been published [8, 16–18]. Of these, three have been published by the same group of authors [8, 17, 18] using a supervised, 3-weeks inpatient exercise program. Although the training adaptations were more favourable during the intensive inpatient training period compared with the subsequent home program, the results of this expensive and impractical exercise training paradigm are difficult to translate to the outpatient rehabilitation models that are widely adopted in Australia and around the world. As a result, to date only one small RCT (*n* = 20) has been published by Chan et al. [16] which examined the impact of exercise training in an outpatient based environment.

Whilst there is preliminary evidence that exercise training improves skeletal muscle oxidative capacity in PH [19], there have been no studies on the effect of exercise training on right ventricular function, overall cardiac function and long-term prognosis. Further robust studies are therefore necessary to assess the efficacy and safety of outpatient-based exercise training programs and to determine the impact of exercise training on cardiac function and prognostic outcomes. As such, the objectives of the present study are to examine the safety and impact of outpatient-based exercise training on cardiac function, and short- and long-term clinical outcomes in medically stable patients with PH. We hypothesise that supervised outpatient-based exercise training is safe for the PH patient population and will result in clinically significant benefits in terms of a reduction in disease severity and delayed time to clinical worsening, as well as improved exercise capacity, QoL and cardiac function.

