#### Primary outcome measure

The primary outcome measure will be exercise capacity assessed using the 6MWT at baseline and following the 8-week study period as per the American Thoracic Society and European Respiratory Society guidelines [22].

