### Sample size and power calculations

A total of 50 participants will be recruited into this study. We have allowed for a 10% drop out over the 8-week period to ensure that 45 participants will complete the study. Where appropriate, sample sizes for the primary and secondary outcome measures have been determined using weighted effect sizes calculated from randomised controlled trials of exercise training in pulmonary hypertension [15].

For the primary outcome measure, i.e. change in the 6MWT distance, the study is powered at 0.91 using a 2-tailed test for independent samples and a weighted effect size of 1.01. For the peak exercise capacity ($$ \dot{\mathrm{V}}{\mathrm{O}}_{2\mathrm{peak}} $$), this study is powered at 0.95 using an pooled, weighted effect size of 1.10 [15]. The primary measure for QoL in the current study will be the CAMPHOR. For the role physical domain in the CAMPHOR, the study is powered at 0.90 based on a weighted effect size of 0.99 [15].

The principle measure for changes in cardiac function will be made using CMRI. Recently Addetia and colleagues suggested that a per group sample size of 23 participants would detect a 5% change in right ventricular ejection fraction [34] measured using CMRI with a power of 80% and the probability of a Type I error of 0.05. The authors suggest that for a 10% change in right ventricular ejection fraction, a smaller sample size of 6 participants would be required. Based on a conservative estimate of a 5% change in right ventricular ejection fraction, the current study would have approximately 80% power to detect changes in right ventricular systolic function.

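### The primary mixed model is not said to condition on baseline 6MWT distance; read naturally it gives a change-score contrast, and stating a baseline-adjusted comparison would gain precision at no cost

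*Protocol article*

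**What the plan says.** - Primary outcome measure section: the outcome is "exercise capacity assessed using the 6MWT at baseline and following the 8-week study period", so there is one measurement before randomisation and one after.
- Sample size and power calculations section: the outcome being powered is the change in walking distance between the two visits, and for it "the study is powered at 0.91 using a 2-tailed test for independent samples and a weighted effect size of 1.01". On numbers: "A total of 50 participants will be recruited into this study" and, allowing for losses, "We have allowed for a 10% drop out over the 8-week period to ensure that 45 participants will complete the study".
- Data analysis section: "We will use a generalised linear mixed model approach which can accommodate missing data points often encountered in longitudinal datasets". The analysis is by intention to treat and uses every available measurement. Other tests are allowed where distributional assumptions fail. "Probability of a Type I error will be set at 0.05".
- Randomisation section: 1:1 allocation in permuted blocks of 10 after the baseline measures; no strata are named.

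The article does not say whether baseline 6MWT distance enters the model as a covariate, as a response with one mean common to both groups, or as a response with a separate mean in each group.

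**The concern.** The outcome is described as a change over two visits, and all measurements go into a longitudinal model whose stated merit is its handling of missing data. Most analysts would fit group, time and their interaction. With two time points and complete data, the interaction estimate from that model is the difference between the groups in mean change. The model estimates a separate baseline mean for each group and makes no use of the fact that randomisation makes those means equal in expectation.

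Two things follow. First, the estimate is less precise than it could be with data the trial already collects. Second, a change score subtracts the whole of any chance baseline difference, whereas only a fraction of it is expected to persist to week 8. The group with the lower baseline is therefore flattered. With about 25 per arm and no strata, such an imbalance is a realistic prospect.

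**Working it through.** **Inputs from the article.** 50 recruited, 10% dropout, 45 completers, 1:1 allocation (hence 22 and 23), two-sided alpha 0.05, standardised effect d = 1.01, stated power 0.91.

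**Assumptions, not in the article.** d is standardised by the SD of change; the SD is the same at both visits; the correlation rho between baseline and week 8 lies between 0.5 and 0.9.

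**Step 1. Reproduce the stated power.** Dropout: 45 / (1 − 0.10) = 50. For a two-sample t-test the noncentrality is d × √(n₁n₂/(n₁+n₂)) = 1.01 × √(22 × 23/45) = 1.01 × 3.353 = 3.39, on 43 degrees of freedom. Power is 0.912, which matches 0.91. The same method returns the other two stated figures: 0.950 at d = 1.10 (stated 0.95) and 0.901 at d = 0.99 (stated 0.90). These figures assume no baseline adjustment.

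**Step 2. Variance with and without adjustment.** With a common SD σ at each visit:
- variance of a change score: 2σ²(1 − rho)
- residual variance after regression on baseline: σ²(1 − rho²)
- ratio, adjusted to change: (1 − rho²) / [2(1 − rho)] = (1 + rho)/2

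The ratio is below 1 whenever rho is below 1.

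**Step 3. Power after adjustment at d = 1.01.** Divide d by √((1 + rho)/2) and use 42 degrees of freedom.

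| rho (assumed) | Variance ratio | Power, change score | Power, adjusted |
|---|---|---|---|
| 0.5 | 0.75 | 0.912 | 0.969 |
| 0.6 | 0.80 | 0.912 | 0.959 |
| 0.7 | 0.85 | 0.912 | 0.948 |
| 0.8 | 0.90 | 0.912 | 0.937 |
| 0.9 | 0.95 | 0.912 | 0.924 |

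The gain is about 1 to 6 points.

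**Step 4. Chance imbalance.** With 25 per arm, the standard error of the difference in baseline means is σ√(2/25) = 0.28σ. Given a baseline difference D, the change-score contrast is shifted by −(1 − rho)D. For D of one standard error, the shift is 0.5 × 0.28σ = 0.14σ at rho = 0.5 and 0.1 × 0.28σ = 0.03σ at rho = 0.9. Baseline adjustment removes this shift.

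**Step 5. How much optimism in d adjustment could absorb.** With 22 and 23 completers, 80% power needs d of about 0.855 without adjustment. Multiplying by √((1 + rho)/2) gives about 0.83 at rho = 0.9, 0.81 at 0.8 and 0.74 at 0.5. Adjustment therefore offsets a 3% to 13% shrinkage in the effect. At an assumed d of 0.7, power is 0.63 without adjustment and 0.65 to 0.75 with it.

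**The case against.** The strongest reply is that the article plans nothing wrong. A reader might infer from the sample-size section that the primary analysis is an independent-samples test of change with no conditioning on baseline. The text does not support that. The independent-samples test belongs to the power calculation, and sizing a trial on a t-test while analysing it with a mixed model is ordinary practice. The Data analysis section does not exclude baseline adjustment, and a mixed model with a common baseline mean fits its wording. A journal article may also leave covariates to a fuller document. All of this stands, so the point cannot be put as an error. What remains is that the endpoint wording and the model named lead naturally to the less efficient contrast.

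A reader might also infer that 0.91 is overstated, because the Background section describes three of the four published trials as inpatient and calls their results "difficult to translate to the outpatient rehabilitation models that are widely adopted". That does not hold as an error either. The power is stated openly as conditional on 1.01. The trials behind 1.01, and their weights, are not listed. The Background's remark on better adaptation compares the inpatient phase with the home phase that followed it, not with supervised outpatient training. The article gives no outpatient effect size, so every value of d below 1.01 is an assumption.

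Finally, the article does not say which SD standardises 1.01. If it were the SD at a single visit, the change-score test would already have power of 0.959 at rho = 0.6 and 0.990 at rho = 0.7, and adjustment would take these to 0.985 and 0.996. The gain in points would be smaller, though still in the same direction.

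**Conclusion.** The point holds as a low-cost improvement in precision. The primary model's handling of baseline is unstated, and its natural reading is a change-score contrast. That contrast has more variance than a baseline-adjusted one, by the ratio (1 + rho)/2, and it leaves part of any chance imbalance in the estimate. At d = 1.01 on the change-score SD, with equal SDs and rho assumed between 0.9 and 0.5, the benefit is a rise in power from 0.912 to about 0.92 to 0.97.

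It should not be read as showing that the plan rejects baseline adjustment, or that the 0.91 is wrong; that figure reproduces without any adjustment. Nor would adjustment rescue the trial from a much smaller effect. Whether an effect of 1.01 carries over to an outpatient programme is a fair question, but a separate one. It is context here.

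**What to change.** In the Data analysis section, state the primary analysis as the between-group difference in week-8 6MWT distance adjusted for baseline 6MWT distance. Either ANCOVA or a mixed model with both visits as responses and a baseline mean common to the two groups would serve; the second keeps the mixed-model approach already named. Use the same form for peak oxygen uptake, CAMPHOR and right ventricular ejection fraction, and keep baseline in any fallback analysis.

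Optionally, add to the power paragraph that 80% power needs an effect size of about 0.855 without adjustment, and that the Background describes three of the four published trials as inpatient. The stated 0.91 need not change.

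The cost is wording only: baseline 6MWT distance is already measured before randomisation, and no change to sample size or visits is needed. Make the change before the data are unblinded, so that the choice of model cannot depend on the results.

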### Randomisation

Eligible participants will be randomised into parallel groups with a 1:1 allocation ratio to either the exercise training group or the control group after completion of the baseline measures. A concealed allocation procedure will be performed by a blinded investigator using permuted block randomisation of 10 subjects and sealed, opaque envelopes. This schedule will ensure a close balance in the number of participants assigned to each group.

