Long term outcomes will be analysed by examining survival and time to clinical worsening during routine follow-up clinic visits for a 2-year period following the participant’s commencement of the study. We will base this measure on the recent PH intervention studies [30–32]. For the purpose of this study clinical worsening will be defined as [30]:PH-related death orlisting for/completed lung transplantation orhospitalization for PH or clinical worsening leading to initiation of new PH-specific treatment orWorld Health Organisation (WHO) functional classification deterioration and a > 15% decrease in 6MWT from baseline.

Participants will be assessed for clinical worsening every 3–6 months following randomisation during routine clinical visits. A panel of two clinical experts, blinded to group allocation, will independently evaluate each participant for clinical worsening. Decisions will be moderated by a third expert, blinded to group allocation, in the event that the panel members reach a different decision.

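### Survival and clinical worsening are timed from the start of exercise or the control period, not from randomisation, which leaves pre-start events and never-starters without a place in an intention-to-treat analysis

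*Protocol article*

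**What the plan says.** The Data analysis section of the protocol article fixes the time origin for the Kaplan-Meier and log-rank analyses: "The commencement of the exercise program or control period will be used as the index date for determining survival or clinical worsening".

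The same section makes a general commitment: "An intention-to-treat analysis will be used to avoid bias in estimating the treatment effect for this superiority study". It then describes who is analysed: "with inclusion of all measures in all available participants, regardless of whether they completed the intervention".

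Under Randomisation, participants are allocated to exercise or to the "control group after completion of the baseline measures". No interval from allocation to the first exercise session is given. The Control group section has controls carry on with routine care for eight weeks, with a weekly call from the coordinator. It does not say which day starts that period.

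Under Secondary outcome measures, clinical worsening is assessed every 3–6 "months following randomisation during routine clinical visits". There the two-year horizon runs from the participant's commencement of the study, and in Data analysis from study commencement. Neither phrase is tied to a date.

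**The concern.** Intention-to-treat compares the groups as randomised, from the moment of randomisation. A time origin that comes later, and that depends on starting the allocated condition, departs from this in two ways.

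- **Events before the start.** A participant who dies or worsens after allocation but before commencement has an event that precedes time zero. Under the rule as written, that event is not counted.
- **Participants who never start.** Someone allocated to exercise who withdraws or worsens before the first session has no commencement date. The inclusion clause protects those who do not complete the intervention; it does not mention those who never begin it.

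The two start events also differ in kind. The exercise clock needs attendance at a supervised outpatient session, whereas the control period continues usual care and has no defined first day. If the exercise start lags further behind randomisation than the control start, more early events are lost from the exercise arm. If those events or non-starters also come from the sicker participants, the comparison shifts towards exercise. About 20 events are expected in all, so one or two that are missed or moved would be visible in the curves.

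**Working it through.** **1. The plan's own figures.** The section on sample size and power gives two-year event-free probabilities of 0.74 (exercise) and 0.36 (control).

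- Risks: 1 − 0.74 = 0.26 and 1 − 0.36 = 0.64.
- Risk ratio: 0.26 / 0.64 = 0.406, reported as 0.41. This reproduces.
- Expected events among 45 participants: 45 × (0.26 + 0.64) / 2 = 20.25.
- The 30% power stated there does not reproduce (a two-proportion formula with 22.5 per arm gives about 74%). That is a separate matter and is not used here.

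The plan gives no figure for the gap between randomisation and commencement. A range of 1 to 8 weeks is **assumed**.

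**2. Hazards, assuming they are constant.** Hazard = −ln(event-free probability) / 2 years.

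- Control rate: −ln(0.36) / 2 = 0.511 per year.
- Exercise rate: −ln(0.74) / 2 = 0.151 per year.

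**3. Expected events before commencement in one arm of 25** (50 recruited, allocated 1:1). Probability of an event in w weeks = 1 − exp(−hazard × w / 52). Each count is divided by the two-year events at the same rate: 25 × 0.64 = 16 (control) or 25 × 0.26 = 6.5 (exercise).

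| Assumed gap | Control rate: probability | Events of 25 | Share of 16 | Exercise rate: probability | Events of 25 | Share of 6.5 |
|---|---|---|---|---|---|---|
| 1 week | 1.0% | 0.24 | 1.5% | 0.3% | 0.07 | 1.1% |
| 2 weeks | 1.9% | 0.49 | 3.0% | 0.6% | 0.14 | 2.2% |
| 4 weeks | 3.9% | 0.96 | 6.0% | 1.2% | 0.29 | 4.4% |
| 8 weeks | 7.6% | 1.89 | 11.8% | 2.3% | 0.57 | 8.8% |

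The control rate is the more natural choice before training has begun. The exercise rate gives the lower end.

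**4. Effect on the test.** A simulation with no treatment effect (25 per arm, 10,000 runs, 0.36 event-free at two years) delayed only the exercise clock and dropped participants whose event came before it started. It used an unstratified log-rank test, because the article does not name the strata. The Monte Carlo standard error near 5% is √(0.05 × 0.95 / 10,000) = 0.2 percentage points.

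| Gap | Constant hazard: two-sided rejection | Front-loaded hazard (Weibull shape 0.7, assumed): rejections favouring exercise | Events dropped, front-loaded |
|---|---|---|---|
| 0 weeks | 5.5% | 2.8% | 0 |
| 2 weeks | 5.5% | 3.9% | 1.6 |
| 4 weeks | 5.0% | 4.9% | 2.5 |
| 8 weeks | 5.1% | 5.9% | 3.9 |

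Under a constant hazard the lost events take their person-time with them, and the test stays near its nominal level. A one-sided tilt appears only when risk is concentrated early. The simulation does not model selective loss of never-starters, which is a separate route to bias; the documents give no basis for sizing it.

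**The case against.** Several stronger readings are tempting, and the documents do not support them.

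- **That early events are lost from the exercise arm only, biasing the result towards exercise.** The rule gives both arms a start date, and the control period is a defined eight weeks with weekly calls. No interval is stated for either arm. If both starts lag equally, the loss falls on both. The eligibility criteria (stable therapy, no recent exacerbation or medication change) also argue against a front-loaded hazard, which is what the simulated tilt required.
- **That intention-to-treat is broken outright.** The index-date sentence excludes nobody in terms, and a condensed article may leave the handling of a never-starter to a fuller document. What stands is that the rule is stated, and as stated it gives such a participant no time origin.
- **That the assessment schedule contradicts the index date.** Counting clinic visits from randomisation and starting the analysis clock elsewhere can coexist. The wording is loose, not contradictory.
- **That 4–29% of exercise-arm events are at risk.** That range comes from dividing control-rate counts (0.24 to 1.89) by the 6.5 events expected at the exercise rate. It mixes two hazards; at matching rates the shares are those in the table.

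Even the table may run high. It applies a registry's two-year rate to selected stable patients, and it spreads a composite evenly over time although clinical worsening is assessed at visits 3–6 months apart. Few events detected only at a visit would be dated before a first session.

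**Conclusion.** The point holds as a design weakness in a stated rule. The clock starts after randomisation and depends on starting the allocated condition, and the plan sets no bound on the time or events that fall before it. The likely size is small: under two expected events in an arm of 25 for a constant hazard and any gap up to eight weeks, and well under one for a gap of a week or two. These figures rest on an assumed gap and on the protocol's own planning probabilities. Bias towards exercise needs two further conditions that the documents neither state nor exclude: a longer lag in that arm, and early events or non-starting related to prognosis. The primary six-minute walk analysis is not touched. The affected endpoint is secondary, and the protocol itself describes it as underpowered and offers it as pilot data. The change is worth making because it costs almost nothing and closes the question.

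**What to change.** In Data analysis, replace the index-date sentence so that survival and clinical worsening are measured from the date of randomisation in both arms, with every randomised participant included and all events from that date counted, whether or not the allocated condition was started. Anchor the two-year horizon, now described by two undated phrases about study commencement, to the same date. An analysis from commencement may be kept as a sensitivity analysis.

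The cost is a sentence or two. No new measurement is needed: allocation is filed when it is made, so the date should already be available.
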